### Sex as a biological variable

We will examine the primary hypothesis and secondary hypotheses with respect to difference by sex. In particular, the primary analysis method will be used and a sex by treatment interaction in the time-averaged odds of engagement in HIV prevention will be added to the model to test whether there are differential treatment effects by sex. With the expected 120 or 1/3 of the sample women, there is reasonable power to uncover a difference.

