### Sample size

Power analyses were generated using the two-group repeated proportions module in PASS 2020 [68] to compute minimum detectable effect sizes for the proposed primary analysis. The study will include 350 participants equally assigned to the intervention and control groups. We assume that as much as 10% of the sample may drop-out at each follow-up; however, we anticipate better retention due to SSP staff engagement in the study [69]. The expected sample sizes at the four follow-ups are thus 315, 284, 255, and 230. Using these sample sizes and assuming α = 0.025, power = 0.80, and that the proportion with PrEP or MOUD engagement will be 30% of the control arm, we computed the minimum detectable odds ratio (OR) 1.56 and absolute proportion difference (pdiff) of 0.101, assuming that all post-intervention time points are part of the contrast. We varied the within-subject correlation ρ from 0.10 to 0.80. Power for a binomial is lowest when the base-rate (control group) probability (P_0_) is near 50%.

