##### *Hypothesis 1*

*C-THR* will be superior to non-SSP clinic referral and patient navigation in promoting engagement in HIV prevention as measured by the proportion of participants taking PrEP and/or MOUD across follow-up at 3, 6, 9 and 12 months post-randomization.

### Primary inferential analyses to address primary hypothesis of objective 1

We hypothesize that, for those randomized to the *C-THR* arm, the odds of our two co-primary outcomes, engagement in PrEP and engagement in MOUD, will be higher than for those randomized to the non-SSP clinic patient navigation, control arm (Hypothesis 1). Generalized estimating equations (GEE) [92] will be used to perform the proposed primary analysis, which is a planned time-averaged comparison of all post-baseline measurements of the each of these outcomes—PrEP: DBS evidence of tenofovir or cabotegravir injection in the previous 8 weeks by electronic health record abstraction; MOUD: UDS with norbuprenorphine or methadone/EDDP; or naltrexone or buprenorphine injection in previous 4 weeks by electronic health record abstraction—across the *C-THR* and control groups to test primary Hypothesis 1. Alpha will be set at 0.025 for this planned comparison to control the Type-1 error across these two co-primary outcomes. In each model, recruitment site (fixed site vs. mobile site) and OUD diagnosis (yes vs. no) will be included in these analyses as required by the stratified randomized design to obtain unbiased results. If the overall test of the intervention is statistically significant, individual contrasts for differences between the conditions at each of the times of follow-up will be performed.

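### The claim of reasonable power for the sex-by-treatment interaction is not supported: on the protocol's own precision, power is about 31% at best for a ratio of odds ratios of 1.56

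*Protocol article*

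**What the plan says.** In the protocol article, the section on sex as a biological variable keeps the primary analysis method and says that "a sex by treatment interaction in the time-averaged odds of engagement in HIV prevention will be added to the model". On the strength of that test it says only: "With the expected 120 or 1/3 of the sample women, there is reasonable power to uncover a difference". It names no interaction size, no significance level and no power figure, and it gives no rule for interpreting a non-significant result.

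The only power calculation is in the Sample size section. "The study will include 350 participants equally assigned to the intervention and control groups". "The expected sample sizes at the four follow-ups are thus 315, 284, 255, and 230". The calculation is made "assuming α = 0.025, power = 0.80, and that the proportion with PrEP or MOUD engagement will be 30% of the control arm", and the result is that "we computed the minimum detectable odds ratio (OR) 1.56 and absolute proportion difference (pdiff) of 0.101". The section adds: "We varied the within-subject correlation ρ from 0.10 to 0.80". It does not say which correlation produced the 1.56.

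For the main comparison, the primary analysis section says: "Alpha will be set at 0.025 for this planned comparison to control the Type-1 error across these two co-primary outcomes". Secondary hypotheses are tested at 0.05. Neither level is assigned to the sex interaction.

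**The concern.** The Sample size section reports the smallest overall effect that reaches 80% power. An interaction contrast between two sexes, one holding about a third of the sample, is estimated with roughly twice the standard error of the overall effect. A design that only just detects an odds ratio of 1.56 overall cannot also have good power for an interaction of that size.

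What is at stake is how the sex analysis will be read. If readers are told in advance that the test is reasonably powered, a non-significant interaction could be misread as evidence that the intervention works similarly in women and men. The design could not support that conclusion unless the true interaction worth excluding were very large.

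**Working it through.** **Inputs from the Sample size section.** 350 participants, 1:1; 315, 284, 255 and 230 followed at the four visits; control proportion 30%; alpha 0.025; power 0.80; minimum detectable odds ratio 1.56, difference 0.101; correlation rho from 0.10 to 0.80.

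**Input from the sex section.** Women: 120/350 = 0.343, or 1/3.

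**Assumptions.** Two-sided tests; exchangeable correlation, the same in both sexes; the same share of women in each arm and at each visit. The alpha for the interaction is not stated, so 0.05 and 0.025 are both shown.

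**Step 1. Reproduce the plan's figure.** With monotone dropout, 230 people contribute four visits, 255 − 230 = 25 contribute three, 284 − 255 = 29 contribute two, and 315 − 284 = 31 contribute one. The effective number of observations is the sum of c·m/(1 + (m − 1)rho), where c people contribute m visits.

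- At rho 0.10: 920/1.3 + 75/1.2 + 58/1.1 + 31 = 853.9.
- At rho 0.50: 920/2.5 + 75/2 + 58/1.5 + 31 = 475.2.

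Using a two-proportion normal approximation at two-sided alpha 0.025, 80% power and rho 0.10, the detectable difference is 0.100 (odds ratio 1.556). With the mean follow-up of 271 at every visit it is 0.101 (odds ratio 1.564). The stated 1.56 and 0.101 therefore reproduce at rho 0.10. If the 0.025 were one-sided, rho of about 0.20 would be needed instead (odds ratio 1.555).

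**Step 2. Main-effect standard error implied by the plan.**
SE(main) = ln(1.56)/(2.241 + 0.842) = 0.4447/3.083 = 0.144.

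**Step 3. Interaction standard error.** With a fraction f of women, the factor is 1/√(f(1 − f)).

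- f = 120/350: factor 2.107, SE = 0.304.
- f = 1/3: factor 2.121, SE = 0.306.

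**Step 4. Power for a ratio of odds ratios of 1.56** (f = 120/350).

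- Alpha 0.05: Φ(0.4447/0.304 − 1.960) = 31%.
- Alpha 0.025: Φ(0.4447/0.304 − 2.241) = 22%.

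With f = 1/3 these are 30.6% and 21.5%. A four-cell logit variance at rho 0.10, with 30% engagement in the control arm for both sexes, gives 31.0% at alpha 0.05 if the larger effect is in women and 30.3% if it is in men.

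**Step 5. Ratio detectable with 80% power.** From the SE in Step 3, at alpha 0.05: exp(2.80 × 0.304) = 2.34. Built from the visit numbers instead:

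| rho | Power for ratio 1.56, alpha 0.05 | Same, alpha 0.025 | Ratio with 80% power, alpha 0.05 |
|---|---|---|---|
| 0.10 | 31% | 22% | 2.35 |
| 0.20 | 26–27% | 18% | 2.55 |
| 0.30 | 23% | 16% | 2.75 |
| 0.50 | 19% | 12–13% | 3.14 |
| 0.80 | 16% | 10% | 3.70 |

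At alpha 0.025 the detectable ratio is about 2.56 at rho 0.10 and 3.52 at rho 0.50.

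**Step 6. What those ratios mean.** Hold the overall odds ratio at 1.56, as a weighted mean on the log scale.

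- No effect at all in women implies an odds ratio in men of exp(0.4447/0.657) = 1.97. Power for that ratio at alpha 0.05 is Φ(0.677/0.304 − 1.960), about 60%.
- A ratio of 2.34 implies about 2.09 in one sex and 0.89 in the other (men and women respectively, if men benefit more), so the effect reverses direction.

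**The case against.** The strongest reply is that the protocol names no interaction size, so nothing stated has been miscalculated, and 1.56 is a benchmark chosen for this check. It is the smallest detectable main effect, not the effect the investigators expect. The background cites PrEP uptake of 0–3% among people who inject drugs, and the discussion cites 59% buprenorphine retention at 3 months in a pilot, so larger effects may be in mind. As an illustration only, 30% engagement in controls with 40% in treated women and 60% in treated men gives a ratio of (1.5/0.4286)/(0.6667/0.4286) = 2.25. Power for that is about 76% at rho 0.10 and 51% at rho 0.50, at alpha 0.05.

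This part stands: the defect is an unsupported description of power, and power is acceptable if the interaction is large enough. It does not rescue the sentence, because the protocol neither states nor justifies an interaction of that size, and even the illustration falls to about a coin toss at a mid-range correlation.

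It is also fair that the test is an effect-modification analysis. It does not enter the sample size, the split of alpha or the primary inference.

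Three stronger readings are tempting but not supported:

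- That the investigators will read a null interaction as showing no sex difference. The protocol sets no such rule; the risk is only that it could be misread.
- That MOUD would fare worse because it would be analysed within the OUD stratum. The planned models include OUD diagnosis as a covariate and do not restrict to that stratum.
- That the power claim has been shown to fail for the secondary outcomes. The section does examine those by sex, but the power sentence follows the description of the engagement interaction, and nothing has been computed for the others.

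**Conclusion.** The statement that 120 women give reasonable power is not supported by the protocol's own figures and should not stand as written. On the precision implied by the Sample size section, power for a ratio of odds ratios equal to the minimum detectable main effect is about 31% at two-sided alpha 0.05, or about 22% if the primary alpha carries over. These are favourable values, because they rest on rho 0.10, the lowest correlation considered. Power of 80% is reached only for a ratio of about 2.35 or more, and about 3.1 at rho 0.50.

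The conclusion rests on two-sided testing, exchangeable correlation and balanced sex shares across arms. Reading the plan's 0.025 as one-sided lowers the 31% to about 26%. The finding concerns the engagement outcomes only.

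**What to change.** Replace the power sentence in the section on sex as a biological variable with wording to this effect: the sex-by-arm test on the primary outcomes is exploratory; at two-sided alpha 0.05 it has 80% power only for a ratio of odds ratios of about 2.35 or more at a within-subject correlation of 0.10, and about 3.1 at 0.50. If the test is to be run at alpha 0.025, the figures are about 2.6 and 3.5. Whichever alpha is used should be stated.

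Add that sex-specific odds ratios will be reported with confidence intervals, and that a non-significant interaction will not be taken as evidence of equal effect in women and men.

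The cost is a few words of text. Sample size, conduct and the primary analysis are unchanged; the only loss is that a stated property of the design becomes less favourable.

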### Interim analyses

If study recruitment fails to meet quotas and the original target sample size appears unlikely to be achieved, investigators will propose an updated target sample size and conduct a futility analysis. Conditional power will be calculated based on the treatment effect size observed in the current data and “information fraction” consistent with the updated target sample size. This analysis indicates the likelihood of finding a significant effect if trends in the current data continue and the updated sample size target is met. If conditional power under the updated sample size fails to meet a pre-specified threshold of 0.5, the stopping rule will be considered satisfied. If, on the other hand, conditional power is high, the trial is likely to meet its primary outcome even with the reduced sample size. The DSMB will use this information to guide its recommendation to continue or discontinue the trial.

### Methods for additional analyses (e.g. subgroup analyses)

We will use the following data analysis plan and statistical procedures to address mediation and moderation.

### Moderation analyses

*C-THR* will buffer the impact of syndemic factors (e.g., unstable housing, food insecurity) on hypothesized outcomes. The GEE model will be used to examine the relationship between syndemic factors and the hypothesized outcomes (see above). Then an interaction between the syndemic factors and treatment assignment will test whether the impact of syndemic factors were lessened in *C-THR*.

### Mediation analyses

The impact of *C-THR* on our hypothesized outcomes will be mediated through reductions in stigma. To maximize rigor, these analyses will not be performed with classical multiple regression-based mediation techniques such as the Baron and Kenny causal steps approach [97]. Instead, mediation analyses will be conducted using structural equation modeling (SEM) and bootstrapped tests of significance of the product of coefficients (a*b, where a is the path coefficient from the intervention to mediator, and b is the path coefficient from mediator to outcome). We will use M*plus* [91] to perform mediation analyses because it unites SEM with causal inference-based mediation methods in the same analysis platform [98]. Alpha will be set at 0.05 for all hypothesis tests in these exploratory analyses.

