## Interventions

### Explanation for the choice of comparators

The CHARIOT study is proposed as an efficacy trial because the study team has already demonstrated the feasibility and acceptability of telehealth for rapid antiretroviral (ART) initiation among PWID and is currently conducting the T-SHARP trial to determine the efficacy of telehealth for HIV care among PWID [40]. *C-THR* will be based out of the IDEA Miami SSP due to its established relationship of trust within the PWID community, and all study participants will be registered clients of the SSP. The study will be a randomized 2-arm trial with participants randomized to either C-*THR* with enhanced telehealth services for PrEP, MOUD, and treatment of HCV, STI or SSTI that can be accessed where the patients are (e.g., SSP, mobile unit, outreach at homeless encampment, or patient home) or to non-SSP clinic referral with a patient navigator. Recruitment will take place at the IDEA Miami SSP and participants will be assessed at 3, 6, 9, and 12 months following randomization to measure PrEP engagement (tenofovir on DBS or abstraction of cabotegravir injection records) or MOUD engagement (norbuprenorphine or methadone on UDS; or abstraction of naltrexone or buprenorphine injection records), as well as syringe coverage, PrEP adherence, HCV treatment engagement, HCV cure, time to injection-related harm and number of injection-related harms. Quantitative assessments will help estimate predictors of engagement in HIV prevention services via the C-*THR* intervention package. Just as with our T-SHARP trial, it is expected that syndemic factors [53, 54] such as unstable housing and/or food insecurity will impact engagement in HIV prevention services across time points and that the C-*THR* intervention will perform better at mitigating the effects of these potential confounders.

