## Data collection and management

### Plans for assessment and collection of outcomes

Data collection for the efficacy analysis is planned at screening, baseline, and at 3-, 6-, 9- and 12-month follow-up assessments (Table 3). All participants will complete quantitative questionnaires in English and Spanish through the secure REDCap platform at baseline, and at 6- and 12-month follow-up assessments. Measures from NIDA’s Data Harmonization projects, specifically PhenX Toolkit [70], will be included. Assessments will take approximately 1 h and include socio-demographics, SUD treatment history, sexual and injection risk behaviors, substances used by injection and other routes of administration, and healthcare service utilization. Importantly, in pursuit of relevant endpoints important for people with SUD, quality of life measures [71, 72] will be assessed in addition to any changes in syndemic factors such as social determinants of health (e.g., employment, housing, food insecurity, incarceration) and mood (e.g., PHQ-9 [73], BAI [74]). We will use the EuroQol 5D (EQ-5D) to measure health-related quality of life [75, 76]. Stigma and discrimination will be measured using the Substance Use Stigma Mechanisms Scale (SU-SMS) [77], the Group-based Medical Mistrust Scale [78], the PrEP Stigma Scale [79], and Physician–Patient Relationship Scale [80].

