Though GEE estimates are consistent even if the correlation structure is misspecified, GEE's statistical efficiency improves as the working correlation structure more closely approximates the actual correlation structure [92], so various correlation structures suitable for the study's design will be considered (e.g., exchangeable, autocorrelated, *m*-dependent, unstructured) [93]. The QIC statistic will be used to select the final correlation structure [94]. Recruitment site (fixed site vs. mobile site) and OUD diagnosis (yes vs. no) will be included in all models as required by the stratified randomized design to obtain unbiased results [95]. Robust standard errors will be used to obtain correct inferences even if the chosen correlation structure remains slightly mis-specified. All analyses will include outlier and influential case screening via computation of GEE-based residual analysis, including leverage, DFBeta, and Cook’s D statistics [96]. If outliers are found, results will be reported with and without outliers included.

### Data analysis plan and statistical procedures to address secondary hypotheses of objective 1

We have proposed several secondary hypotheses related to the *C-THR* intervention. The secondary analyses will use exactly the same preliminary analysis and missing data strategy as Hypothesis 1. In secondary analyses, we will examine the distributions of syringe coverage, PrEP adherence, HCV treatment engagement, HCV cure, STI treatment uptake, and number of injection related harms and assess time to first injection-related harm between the intervention and control groups. GEE [92] will be used to perform the proposed secondary analysis, which is a planned time-averaged comparison of all post-baseline measurements of the each of these outcomes. Statistical procedures for these secondary hypotheses will follow the same strategy used for the primary hypothesis. The alpha will be set at 0.05 for each these secondary hypotheses. In each model, recruitment site (fixed site vs. mobile site) and OUD diagnosis (yes vs. no) will be included in these analyses as required by the stratified randomized design to obtain unbiased results. To maximize rigor, appropriate diagnostics including outlier and influential case screening will be examined for each model. If outliers are found, results will be reported with and without outliers included.

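### The exploratory bootstrapped a*b test can be significant without causal mediation through stigma, because the stigma-to-engagement path is not randomised and no adjustment for common causes is named

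*Protocol article*

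**What the plan says.** All references are to the protocol article.

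- **Mediation analyses.** The hypothesis is causal: "The impact of *C-THR* on our hypothesized outcomes will be mediated through reductions in stigma". The test is a structural equation model with "bootstrapped tests of significance of the product of coefficients", where "b is the path coefficient from mediator to outcome". No covariates are named for either path. Mplus is chosen "because it unites SEM with causal inference-based mediation methods in the same analysis platform". The analyses are labelled exploratory, with alpha 0.05.
- **Explanation for the choice of comparators.** Syndemic factors such as unstable housing and food insecurity are expected to affect engagement, and C-THR "will perform better at mitigating the effects of these potential confounders".
- **Moderation analyses.** This is where syndemic factors are given an analytic role, as moderators of the treatment effect.
- **Plans for assessment and collection of outcomes.** Questionnaires are planned at baseline, 6 and 12 months. In them, "quality of life measures [71, 72] will be assessed in addition to any changes in syndemic factors such as social determinants of health"; PHQ-9, BAI and several stigma scales are listed too.
- **Primary inferential analyses.** Recruitment site and OUD diagnosis "will be included in all models as required by the stratified randomized design". Under Preliminary analyses and missing data, predictors of missingness are added, but for the primary hypothesis tests.

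**The concern.** The product a*b combines a randomised contrast (a: arm to stigma) with an observational association (b: stigma to engagement, given arm). A participant in unstable housing may both feel more stigma and be less able to stay on PrEP or MOUD. Unless such a factor is in the model, b differs from zero even if stigma does nothing. The bootstrap describes sampling error in a*b and keeps every common cause in each resample.

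The null being tested is therefore that C-THR does not move stigma, or that stigma is unassociated with engagement given arm and whatever else is in the model. The stated hypothesis is narrower: that stigma carries part of the effect. For a programme built to reduce stigma, path a may well be real, and the conclusion then depends on b. At stake is a published claim that stigma reduction is the mechanism.

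Choosing software that supports causal mediation methods does not settle this. Those methods also need the mediator-outcome confounders in the model, and the section names no confounder set, no causal assumption and no sensitivity analysis.

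**Working it through.** **Figures from the plan.** None is given for mediation. The inputs borrowed from Sample size check out:

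- Ten per cent loss per visit: 350 × 0.9 = 315; × 0.9 = 283.5 (stated 284); × 0.9 = 255.15 (255); × 0.9 = 229.6 (230).
- OR 1.56 on a 30% control rate: odds 1.56 × 0.30/0.70 = 0.669, so 0.669/1.669 = 0.401, a difference of 0.101 as stated.

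**Assumptions (not in the documents).** A binary common cause U with 50% prevalence raises stigma by g residual SDs and lowers the log-odds of engagement by the same g. C-THR lowers stigma by a residual SDs. Arm has a direct effect of OR 1.56. Stigma has no effect on engagement (true b = 0), and engagement has no effect on stigma.

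**Hand approximation, n = 284, a = 0.5.** Average engagement is (0.300 + 0.401)/2 = 0.35, so n·p(1−p) = 284 × 0.35 × 0.65 = 64.6. Var(U) = 0.25. With U left out:

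- Var(stigma | arm) = v = 1 + 0.25g²
- Spurious b ≈ −0.25g²/v
- SE(b) ≈ 1/√(64.6·v)
- SE(a) ≈ 2√v/√284

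| g | v | spurious b | SE(b) | abs(z) for b | P(b significant) | abs(z) for a | P(a significant) | product |
|---|---|---|---|---|---|---|---|---|
| 0.5 | 1.0625 | −0.059 | 0.121 | 0.49 | 7.8% | 4.09 | 98.3% | 7.6% |
| 0.8 | 1.16 | −0.138 | 0.116 | 1.19 | 22.3% | 3.91 | 97.5% | 21.7% |
| 1.0 | 1.25 | −0.200 | 0.111 | 1.80 | 43.6% | 3.77 | 96.5% | 42.0% |

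Each probability is the two-sided normal one at 1.96. The product treats the two tests as independent.

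**Simulation.** 600 trials per row; least squares for a, logistic regression for b given arm, 95% Monte Carlo interval for a*b.

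| n | a (SD) | g | U omitted | U included |
|---|---|---|---|---|
| 284 | 0.5 | 0 | 3.7% | 3.8% |
| 284 | 0.5 | 0.5 | 8.3% | 6.2% |
| 284 | 0.5 | 0.8 | 21.3% | 3.0% |
| 284 | 0.5 | 1.0 | 40.7% | 2.8% |
| 284 | 0.3 | 0.5 | 2.0% | 1.7% |
| 284 | 0.3 | 0.8 | 9.5% | 3.7% |
| 284 | 0.3 | 1.0 | 23.2% | 3.8% |
| 350 | 0.5 | 0.8 | 24.7% | 4.3% |
| 350 | 0.5 | 1.0 | 43.7% | 5.7% |

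The standard error at 21.3% is √(0.213 × 0.787/600) = 1.7 points. A percentile bootstrap at n = 284 and a = 0.5 agreed: 20.5% against 2.0% for g = 0.8 (200 trials), and 37.3% against 5.3% for g = 1.0 (150 trials). With a = 0 the rate never exceeded 1.3%. Under moderate or strong confounding nearly all false findings were in the hypothesised direction.

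**The case against.** **Silence is not a choice.** The section lists no covariates, and an article may leave them to the full protocol or analysis plan. That stands: a reader might infer that the model will be unadjusted, and the document does not say so. Site and OUD are set as a minimum, in a section about the primary analysis. What remains is the stated content. Significance of a*b is made the test of a causal claim, while the factors called potential confounders are given a role only as moderators.

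**The authors point to causal methods.** This suggests that more than a bare a*b test may be intended, but it is given as a reason for choosing software.

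**Syndemic factors are not said to drive stigma.** Correct. The comparator section links them to engagement and speaks of C-THR mitigating their effects, which is moderation. The link to stigma is plausible, but it is supplied here.

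**The test does not always reject.** A reader might infer that a*b becomes significant whenever C-THR lowers stigma and stigma correlates with engagement. That is true only as the sample grows; here most scenarios reject in well under half of trials.

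**Adjustment works by construction.** In the simulation U is fixed and fully measured. Under Intervention description, peer counsellors also help with housing and food insecurity, so these may change after baseline because of treatment. Baseline covariates do not remove that part.

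**Conclusion.** The concern holds in limited form. As described, a significant a*b does not establish mediation through stigma, because randomisation does not protect the b path and no adjustment for its confounders is named. With a 0.5-SD stigma reduction at n = 284, the false-mediation rate is near nominal under weak confounding and roughly 20% to 40% under moderate to strong confounding. With a 0.3-SD reduction it is 2% to 23%. All these rates rest on assumed effect sizes, so they show what could happen and do not predict this trial. The analysis is exploratory, and the primary comparison and its alpha do not depend on it. The change is still worth making, because the variables are already planned and the result would be read as a mechanism.

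**What to change.** In Mediation analyses:

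1. State that both the stigma and the engagement equations include the baseline value of the stigma scale used as mediator, baseline syndemic factors (for example housing and food insecurity), baseline PHQ-9 and BAI, and the site and OUD strata.
2. Report a sensitivity analysis over a stated range of residual correlation between the mediator and outcome errors, giving the value at which the indirect effect vanishes.
3. Describe a significant a*b as consistent with mediation, and note that baseline adjustment does not cover confounders that C-THR itself changes.

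The cost is a few sentences, one extra exploratory analysis and possibly a slightly wider interval for b. On the text of the data collection section no new data are needed; the assessment schedule in Table 3 should confirm that these measures are taken at baseline.
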